#### Secondary outcomes

##### Pulmonary function

FVC and DLCO% will be examined at baseline and at the end of the treatment. A positive change will indicate the improvement of pulmonary function.

##### All-cause mortality

Any death for IPF patients in this study with any cause will be recorded and counted. All-cause mortality will be calculated at the end of the treatment in each group. A lower number in the experimental group indicate a better efficacy for the intervention in improving prognosis.

##### Clinical symptoms and signs

Assessment will be performed by a clinical symptom assessment questionnaire. The clinical symptoms to be evaluated in this study include cough, expectoration, chest tightness, shortness of breath, wheezing, and cyanosis. A score of 0–3 will be given to every symptom or sign with a higher score indicating a worse condition.

##### Dyspnea

Dyspnea will be assessed by the Modified Medical Research Council (mMRC) scores set up by the American Thoracic Society [30]. A score of 0–4 will be given according to the degree of immediate dyspnea. A higher score indicates worse dyspnea.

##### Health-related quality of life

HRQoL will be assessed by the COPD Assessment Test (CAT), St. George’s Respiratory Questionnaire (SGRQ), 36-Item Short-Form Health Survey (SF-36), and A Tool to Assess Quality of life in IPF (ATAQ-IPF), with a higher value indicating a better HRQoL for SF-36 and a worse HRQoL for CAT, SGRQ, and ATAQ-IPF. CAT [31], which includes 8 items with a value of 0 to 5 for each item, is a self-assessment questionnaire commonly used in COPD evaluation. Because of the similarity of the assessment symptoms, it was adopted in this study. SF-36 [32], which includes 36 items in 8 domains, is a universal scale for the assessment of health impairment in a wide range of field. SGRQ [33], with 50 items in 3 domains, is widely adopted to assess health impairment for respiratory diseases. The total scores of SGRQ and SF-36 will be counted by weighing of each item. ATAQ-IPF is an IPF-specific questionnaire to assess the HRQoL of IPF patients. There are 13 domains and 74 items with a score of 1–5 for each item in ATAQ-IPF [34]. All the questionnaires will be completed by the patients themselves. Patients should choose an option which is most consistent with their current condition for each item. If necessary, the researchers could provide help. Then, the researchers complete the scoring.

#### Safety outcomes

We will also evaluate the safety of interventions in this study. Safety outcome measures, including routine blood, urine, and stool tests; liver and kidney function tests; and electrocardiography, will be examined. Any adverse events will also be recorded and managed according to the degrees of damage at any time they occur during the treatment period. Then, we will also report to the ethics committee for further management. Based on our previous studies, the possible adverse events are transient gastrointestinal discomfort without the need for intervention.

Pulmonary function, routine blood, urine and stool tests, liver and kidney function tests, and electrocardiography will be tested and recorded at baseline (week 0), at 6 months after treatment (week 26), and at the end of the treatment (week 52). 6MWT, clinical symptoms and signs, MMRC, CAT, SF-36, SGRQ, and ATAQ-IPF will be completed and recorded at week 0, week 13, week 26, week 39, and week 52 in the process of trial.

##### Quality control

To help improve the quality of research, different quality control measures will be adopted throughout the whole process. Before the study, a research team including clinicians, statisticians, ethicists, pathologists, and radiologists has been set up to discuss and form the study protocol, and standard operating procedures (SOPs) for each step of the trial, such as registration, recruitment, and visit for all the enrolled patients, have also been formulated by the research team to ensure the accuracy and completeness of the obtained data in the trial. Every researcher in each center will be trained on the SOPs. The research procedures, completion and normalization of case report forms (CRFs) in each center will also be examined periodically by independent researchers, which is another important means to help improve research quality.

##### Data management and statistical analysis plan

Statistical analysis will be conducted both in the intent-to-treat (ITT) and pre-protocol (PP) data. ITT analysis will be applied to analyze the safety data. All the data from any included patients will be analyzed regardless of their withdrawal from the trial. The PP analysis will be adopted to assess the efficacy of the interventions. If data permit, sub-group analysis will also be performed to help clarify the therapeutic effect of interventions.

All the *P* values will be set as two-tailed with a significant level of 0.05. Measurement data will be shown with mean ± SD, median, and inter-quartile range. Count data will be presented by frequency or composition ratio. Analysis of variance (ANOVA) will be used to test for the differences in continuous variables, with the chi-square test for categorical variables. If necessary, the paired *t*-test will be applied to intra-group comparison data with normal distribution and homogeneous variance, and the Wilcoxon signed-rank sum test will be used for non-normal distribution or uneven variance. Repeated-measures ANOVA will be used to test the continuous response variables that are measured at more than two time points for the same patient, such as 6MWT, clinical symptoms and signs, mMRC, and HRQoL. To improve the quality of data, all the data management and statistical analysis will be conducted by the Jiangsu Famous Medical Technology Co., Ltd. in Nanjing, China.

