#### Eliminated criteria

The enrolled patients will also be withdrawn for any of the following criteria: (1) poor adherence to medication with rates of less than 80% or more than 120%, (2) taking any drug prohibited in this program, and (3) discontinued the given drugs themselves. According to our previous study, the withdrawing rate will be not higher than 20%. All the records for all the eliminated patients will also be preserved.

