### Procedures and interventions

Patients in the experimental group will be treated with JHG for 52 weeks, while the control group are treated with a JHG placebo. JHG is a Chinese herbal compound medicine. The compounds of one dosage for JHG are found in Table 1. The placebo used in this study will contain 5% of the same components of JHG. All the JHG and placebo will be produced and packed by Jiang Yin Tian Jiang Pharmaceutical Co. Ltd., Jiangsu, People’s Republic of China, without any difference in the appearance, color, smell, and weight. The drug quality will be tested by the organization with specific qualifications before application and consistent with the required quality standards. Each dosage of JHG granules or placebo has been produced and packed into 4 bags with 10.9 g per bag (Batch number: 2006337). JHG or JHG placebo will be prescribed 2 bags each time, twice a day orally with 5 days on and 2 days off.

**Table 1 Tab1:** Components of Jin-shui Huan-xian granules

Chinese name	Latin name	Parts of the substances	Amount (g)
Ren Shen	*Radix Ginseng*	Root	6
Shu Di Huang	*Rehm,annia glutinosa Libosch*	Root tuber	12
Mai Dong	*Ophiopogon japonicus*	Root tuber	9
Gua Lou	*Trichosanthes kirilowii Maxim*	Mature fruit	9
Zhe Bei Mu	*Fritillaria thunbergii Miq*	Bulb	9
Mu Dan Pi	*Paeonia Suffruticosa Andrew*	Root bark	9
Zhi Yin Yang Huo	*Epimedium brevicornu Maxim*	Whole herb	6
Chao Bai Guo	*Ginkgo biloba L*	Mature seed	9
Chen Pi	*Citrus reticulata Blanco*	Peel of fruit	9
Zhi Gan Cao	*Glycyrrhiza uralensis Fisch*	Root and rhizome	9

At the same time, all the patients will also be treated with conventional modern medicine. Considering the side effects and costs, the application of pirfenidone and nintedanib will not be limited uniformly. During the whole procedure, all the patients will be visited every 13 weeks and receive given physical examinations. Blood and urine samples and exhaled breath condensate will be collected with the participants’ consent for further researches. If patients are under AE, the Chinese medicine granule or placebo will be suspended until the condition becomes stable. To improve the patients’ adherence, the remaining drugs and empty bags will also be returned except for regular telephone follow-up. The whole procedure for each patient is found in Fig. 2.

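### Efficacy is assigned to the per-protocol set and intention to treat is given no efficacy role, so the efficacy conclusion would rest on a set selected after randomisation

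*Protocol article*

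**What the plan says.** The section Data management and statistical analysis plan opens with "Statistical analysis will be conducted both in the intent-to-treat (ITT) and pre-protocol (PP) data" (the printed term evidently means per-protocol). It then gives each set a task. For intention to treat: "ITT analysis will be applied to analyze the safety data". Next comes "All the data from any included patients will be analyzed regardless of their withdrawal from the trial", which by its position describes the intention-to-treat set. For the other set: "The PP analysis will be adopted to assess the efficacy of the interventions". No sentence names intention to treat as a primary or sensitivity analysis of efficacy.

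The article gives no separate definition of the per-protocol set. The nearest thing is the section Eliminated criteria, which withdraws enrolled patients for "poor adherence to medication with rates of less than 80% or more than 120" per cent, for use of a prohibited drug, or for stopping the study drug themselves. It expects no more than 20% withdrawal and says the records will be preserved.

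Two other sections bear on this. Procedures and interventions says: "If patients are under AE, the Chinese medicine granule or placebo will be suspended until the condition becomes stable". In that sentence AE means acute exacerbation, and the section Exacerbations of IPF makes the number of exacerbation-related hospitalisations over the year a primary outcome.

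**The concern.** The trial compares JHG with placebo and sets out to show benefit. Randomisation makes the two arms comparable only for the patients as randomised. All three elimination criteria arise after randomisation, and each may depend on treatment, on tolerability or on how the patient is doing. In a progressive disease, patients who stop may well be those who are deteriorating. Deterioration is also what the primary outcomes measure: exacerbations, 6-minute walking distance (6MWD) and progression-free status.

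If efficacy is judged on the patients who remain, a difference between arms may reflect who was removed and not what the drug did. Every efficacy conclusion depends on this choice. The article states the choice outright, so it is not a detail left to an analysis plan.

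**Working it through.** **1. How many patients are involved.** Inputs from Sample size and Eliminated criteria: 312 patients, 156 per group, 20% loss.
- 0.20 × 312 = 62.4, so about 62 randomised patients could be left out of the efficacy comparison.
- The article's own step from 124 to 156 per group follows from the 20%: 124 / 0.80 = 155, within one patient of the stated 156.

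**2. When exclusion biases the comparison.** Suppose there is no true effect. In an arm that excludes a fraction f, let the excluded patients average g metres less on 6MWD than those retained. The retained mean then lies f × g above the mean of the whole arm, and the bias in the per-protocol difference is f_E × g_E − f_C × g_C.
- Equal and alike (20% in each arm, same g): the bias is 0 and the two-sided error rate stays at 5.0%.
- Unequal numbers (25% against 15%, which average 20%), with g assumed to be 30 to 90 m: bias = 0.10 × g = 3 to 9 m in favour of the arm that loses more. The pooled SD is √((87.67² + 81.18²)/2) = 84.49 m and the retained numbers are 117 and 132.6. The standard error is 84.49 × √(1/117 + 1/132.6) = 10.72 m, and the false-positive rate is 5.9% to 13.4%.
- Equal numbers but different prognosis (20% each, g of 60 m against 30 m, assumed): bias = 0.20 × 30 = 6 m. Equal counts alone are therefore no safeguard.

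The fractions and gaps by arm are assumptions; the article gives none. For scale, the difference used for sample size is 374.38 − 342.57 = 31.81 m.

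**3. Whether an exacerbation can itself lead to exclusion.** With 5 dosing days a week for 52 weeks there are 260 dosing days. Twenty per cent of these is 52 days, or 52 / 5 = 10.4 weeks. A patient who is otherwise fully adherent falls below 80% only when more than 52 dosing days are suspended, and only if suspended days count as missed. The article does not say whether they do.

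**4. What intention to treat does to 6MWD power.** Power is two-sided at 0.05, approximately Φ(δ / (SD√(2/n)) − 1.96), with SD 84.49 m.

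| Set | n per group | Difference (m) | Power |
|---|---|---|---|
| Per-protocol | 124 | 31.81 | 84.2% |
| Intention to treat, full effect in all | 156 | 31.81 | 91.4% |
| Intention to treat, 20% keep half the effect (assumption) | 156 | 31.81 × 0.90 = 28.63 | 84.9% |
| Intention to treat, 20% keep none (assumption) | 156 | 31.81 × 0.80 = 25.45 | 75.8% |

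The intention-to-treat rows assume that outcomes are obtained for all 156. Separately, 124 per group does not follow from the β of 0.01 printed in Sample size, which would need 260 per group. That is a different matter and does not affect the table.

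**The case against.** Several points on the other side are sound.

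- **Intention to treat is not ruled out for efficacy.** The opening sentence says both sets will be analysed, and nothing says that intention to treat serves safety only. A reader might infer that it is reserved for safety; the text does not go that far. It does give efficacy to the other set and leaves intention to treat without an efficacy task, so the defect stands.
- **Exclusion through exacerbation is not stated.** A reader might infer that patients whose drug is suspended leave the efficacy set, so that exacerbation rates are understated in both arms. The documents do not support this as a fact. Suspension directed by the protocol differs from a patient stopping the drug, and the adherence denominator may be defined in the full protocol or analysis plan. The link is conditional.
- **The per-protocol definition is inferred.** The article does not say that the elimination criteria define the set. They are the only such criteria it offers.
- **Bias is possible, not shown.** The suspension and adherence rules are the same in both blinded arms. Nothing in the article indicates unequal exclusion, and any figure for a spurious effect depends on assumed inputs.
- **The 20% is a ceiling on withdrawal and a drop-out allowance, not a planned exclusion.** Part of it may be patients lost to follow-up, whose outcomes intention to treat would not recover.

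The article also never uses the word superiority. That reading follows from the placebo control and from the stated expectation of fewer exacerbations under JHG, and it is fair.

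**Conclusion.** The plan is wrong as written on which set decides efficacy. It assigns efficacy to the per-protocol set, and its apparent definition of that set removes randomised patients for adherence, prohibited drugs or self-discontinuation. Up to about 62 of 312 patients could be affected. The resulting comparison is not protected by randomisation. Its bias could favour either arm if exclusions differ between arms in number or prognosis, and is nil if they are equal and alike.

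This conclusion rests on one inference, that the elimination criteria define the per-protocol set. It does not depend on the exacerbation link. That link would add a route by which a primary outcome event leads to exclusion, but only if suspended days lower the adherence rate and more than 52 dosing days are lost. The documents do not show that the result would be biased towards JHG, or by how much.

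**What to change.** In Data management and statistical analysis plan, replace the two sentences that assign the sets with wording such as: *The primary efficacy analysis of all primary outcomes is by intention to treat, including all randomised patients as randomised and using all outcome data collected whatever the adherence. The per-protocol analysis is supportive; its exclusions are fixed in a blinded review before unblinding.*

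Two further changes are needed to make this work:
- In Eliminated criteria, state that patients who meet these criteria stay in scheduled outcome follow-up where they consent. At present they are withdrawn and their records kept, but no sentence says that later outcomes are collected.
- Reconcile Eliminated criteria with Procedures and interventions on how days of suspension during an acute exacerbation enter the adherence rate.

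The cost is more than a change of wording, because some patients must be followed further, though at visits already planned. The intention-to-treat estimate may be somewhat smaller than the per-protocol one. No extra enrolment is needed to match the present 84.2% power for 6MWD if non-adherers keep at least half the effect; power falls below that if they keep none. The article reports 70 patients enrolled at submission. The follow-up instruction gains most from being issued early, and the choice of analysis set must be settled before unblinding.

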## Anticipated results

Based on our previous study, it is hypothesized that JHG will reduce the frequencies of acute exacerbations; improve exercise capacity, pulmonary function, and quality of life; and delay the disease progression-free. High-level evidence-based support for traditional Chinese medicine in idiopathic pulmonary fibrosis will also be obtained in this study.

## Discussion

TCM has a long history and certain efficacy in the treatment of respiratory diseases. However, there was still no consensus for disease name and core pathogenesis of IPF in TCM, which also limits the clinical application. We have also conducted abundant researches in TCM for IPF. Based on the summary of the literatures and clinical experience, we hold that IPF should be treated by referring to *feiwei* or *feibi* in TCM [35].

We have also conducted an exploratory trial to evaluate the efficacy and safety of TCM treatment based on syndrome differentiation preliminarily. The results preliminarily clarified the efficacy and safety of TCM treatment based on syndrome differentiation and provide evidence-based support for TCM in IPF. However, the interventions were given according to the different patterns of syndrome differentiation. It may be difficult for clinical application, especially for non-TCM doctors. For TCM, treatment based on syndrome differentiation has been the critical method for thousands of years. In general, TCM doctors will discriminate the different patterns of syndromes first according to the clinical performance and characteristics. However, clinical performance and characteristics are atypical, which would limit TCM syndrome differentiation, and the sample size is small, which will limit the level of evidence. Therefore, to obtain high-level evidence-based support and apply it conveniently, further confirmatory study for core TCM pathogenesis and Chinese medicine is urgent. As we also know, this is the first multi-centers large-sample randomized controlled trial to clarify the efficacy and safety of Chinese herbal medicine.

In recent years, different studies have shown the efficacy and safety of TCM for IPF [36, 37]. Most of them were small-sample studies with a deficiency of standard design and research procedures for high-level evidences. Evidence-based supports of TCM for IPF have not been well-presented. The clinical application has also been limited. In view of these deficiencies, we adopted a design of standard RCT based on the discussion and conclusion of the previous studies. The international standard study procedure, such as trial registration, patient enrollment, and follow-up, has also been adopted. To further improve the quality of the study, related SOPs have also been formulated. In the future study process, the implementation of SOPs will be examined and discussed periodically. If necessary, we will adjust the part of unsuitable contents according to the actual state. We believe that this study will also provide some references for the TCM standard researches.

Our previous study has revealed the possible active components and potential targets for JHG in the treatment of IPF [38]. A total of 136 compounds from JHG and 265 potential targets have been found. The compounds could exert a synergistic effect by regulating these similar targets probably. JHG could also ameliorate pathological changes and collagen deposition in bleomycin-induced pulmonary fibrosis rats [23], and inhibited NADPH oxidase 4 (NOX4) levels and increased the nuclear factor erythroid 2-related factor 2 (Nrf2) in lung tissues could also be found. In vitro, transforming growth factor β1 (TGF-β1)-induced differentiation of fibroblasts could also be significantly inhibited by JHG. So, we concluded that JHG may show long-term effects in bleomycin-induced pulmonary fibrosis rats. The clinical efficacy of JHG will also be confirmed by the results of this study.

However, there are still some limitations to this study. This study aims to the core TCM pathogenesis and Chinese medicine for IPF. TCM treatment based on syndrome differentiation is not taken into account. The actual advantages of TCM, such as individualized treatment, will be discounted. However, it is unavoidable under the current research conditions. Combined with studies with other design types, such as cohort studies, the advantages of TCM may be presented better at different levels.

Based on our previous research, this study will confirm the hypothesis that JHG could reduce acute exacerbation, improve exercise capacity, delay disease progression, and improve pulmonary function and quality of life for IPF patients with sound safety. The results will provide high-level evidence-based supports for TCM in the treatment of IPF. The study design will also provide critical references for TCM studies on core pathogenesis.

## Trial status

At the moment of manuscript submission, 70 IPF patients have been enrolled in this study and recruitment is in progress.

## Data Availability

Data availability is not applicable for this article as no datasets have been generated or analyzed during the current stage.

## Abbreviations

6MWD: Six-minute walking distance
AE: Acute exacerbation
ANOVA: Analysis of variance
ATAQ-IPF: A Tool to Assess Quality of life in IPF
CAT: COPD assessment test
DLCO%: Diffusing capacity percentage of the predicted value
FVC: Forced vital capacity
HRQoL: Health-related quality of life
ILD: Interstitial lung disease
IPF: Idiopathic pulmonary fibrosis
JHG: Jin-shui Huan-xian granule
mMRC: Modified Medical Research Council
RCT: Randomized controlled trial
SF-36: 36-Item Short-Form Health Survey
SGRQ: St. George’s Respiratory Questionnaire
SOPs: Standard operating procedures
TCM: Traditional Chinese medicine
